**Background and Rationale**

Most people with COVID-19 experience mild symptoms or moderate illness. Approximately 10-15% of cases progress to severe disease, and about 5% become critically ill. Typically people recover from COVID-19 after 2 to 6 weeks. For some people, some symptoms may linger or recur for weeks or months following initial recovery. This can also happen in people with mild disease. People are not infectious to others during this time but are unable to return to their normal life. Some patients develop medical complications that may have lasting health effects. This prolonged illness after COVID-19, are seen even in young adults without underlying co-morbidities. There are many case reports from people who do not regain their previous health for a longer period following COVID-19. Risk factors for persistence of symptoms could be hypertension, obesity and mental health conditions.^1^

Little is known about the clinical course of COVID-19 following milder illness. Lingering symptoms reported by participants of a multi-state phone study in the USA included fatigue, cough, congestion or shortness of breath, loss of taste or smell, headache, body ache, diarrhea, nausea, chest or abdominal pain and confusion. In this survey of symptomatic adults who had a positive outpatient test result for SARS-CoV-2, 35% had not returned to their usual state of health when interviewed 2–3 weeks after testing. 20% (1 in 5) among those 18 to 34 years in good health, reported that some symptoms were prolonged and symptoms least likely to have resolved included cough, fatigue and shortness of breath. This report indicates that even among symptomatic adults tested in outpatient settings, it might take weeks for resolution of symptoms and return to usual health.^2^ In contrast, over 90% of outpatients with influenza recover within approximately 2 weeks of having a positive test result.^3^ Factors like old age and presence of multiple co-morbidities among adults hospitalized with COVID-19 are also associated with prolonged illness in an outpatient population. Notably, convalescence can be prolonged even in young adults without chronic medical conditions, potentially leading to prolonged absence from work, studies, or other activities.^2^

The previous corona virus outbreaks of SARS in 2002 and MERS in 2012 has reported reduced lung function and exercise capacity at six months post-discharge and post-traumatic stress disorder, depression, anxiety and reduced quality of life at one year were observed. A prospective cohort study performed on the long term effects of severe acute respiratory syndrome (SARS) epidemic emerged in 2003 showed that, 52% of SARS survivors had persistent impairment in diffusing capacity of the lungs for carbon monoxide and that exercise capacity and health status were significantly lower than the normal controls of the same age groups at 24 months post-illness.^3^ Another study, revealed that 40% of people recovering from SARS still had Psychiatric morbidities and chronic fatigue symptoms even 3.5 years after being diagnosed and so optimization of the treatment of mental health morbidities by a multidisciplinary approach with a view for long-term rehabilitation especially targeting psychiatric and fatigue problems, would be needed in the survivors.^4^

COVID-19 is presenting with a wide spectrum of clinical symptoms like severe respiratory dysfunction, septic shock and multiple organ dysfunction or failure etc. Body systems and organs that can be affected after the COVID-19 infection are heart (damage to heart muscle, heart failure), lungs (damage to lung tissue and restrictive lung failure), brain and the nervous system [loss of sense of smell (anosmia)], consequences of thrombo-embolic events such as pulmonary embolism, ischemic heart disease, stroke, cognitive impairment (e.g. memory and concentration), affected mental health (anxiety, depression, post-traumatic stress disorder and sleep disturbance), musculoskeletal symptoms (pain in joints and muscles) and fatigue are common conditions observed.^1^The problems faced by survivors of COVID-19 after recovery are getting reported now. More time and research is needed to understand the long-term effects of COVID-19, why symptoms persist or recur, how these health problems affect patients, the clinical course and likelihood of full recovery.A study has reported that high proportion of individuals of COVID-19 recovered reported fatigue, dyspnoea, joint pain and chest pain.^5^Health-related quality of life was poor among COVID-19 patients at the 1 month follow-up and patients suffered from significant physical and psychological impairment.^6^ Therefore, prospective monitoring of individuals exposed to SARS-CoV-2 is needed in order to fully understand the long-term impact of COVID-19, as well as to inform prompt and efficient interventions to alleviate suffering. Also there is an urgent need to address the issues of survivors of COVID-19 for their rehabilitation in terms of disease/ treatment induced complications, secondary prevention, mental/ psychosocial impact, and overall quality of life. As per the National Clinical Management Protocol based on Ayurveda and Yoga for management of COVID-19 issued by Ministry of AYUSH, Govt. of India, Ayurvedic *Rasayana* such as Ashwagandha and Yoga have been suggested for post-COVID management. Noticeably, the combination of Agastya Haritaki and Ashwagandha along with Yoga have the advantages of simplicity, affordability, and may be easily acceptable among society to fight against post COVID-19 condition. So this study has been designed to see the efficacy of Ayurveda interventions and Yoga in rehabilitating the patients suffering from prolonged effects of COVID-19.

**Objective(s)**

Primary Objective

- To assess the efficacy of Ayurveda interventions and Yoga in rehabilitation of COVID-19 cases suffering with long term effects of COVID-19 as compared to WHO Rehabilitation Self-Management after COVID-19- Related Illness

Secondary Objective

- To assess the safety of the Ayurvedic interventions in cases suffering with long term effects of COVID-19

**Study Design**

- Open label Randomized Controlled Multi-centric Trial with a study period of 90 days from the day of enrolment.
- 2-arm, parallel group exploratory study with 1:1 allocation ratio

**Study Setting**

- Two Academic Hospitals situated in Maharashtra, India viz. Government Medical College and Hospital, Nagpur and Datta Meghe Institute of Medical Sciences (Deemed as University),Wardha

**Eligibility Criteria**

**Inclusion criteria:** Patients of either sex between 18 to 60 years, ambulatory, willing to participate, with history (not more than 4 weeks) of positive RT-PCR for COVID-19 or IgM antibodies positivity for SARS CoV-2, but having negative RT-PCR for COVID-19 at the time of screening will be considered eligible for enrolment in the study.

**Exclusion criteria:** Critically ill patients with ARDS (acute respiratory distress syndrome), requiring invasive respiratory support in the intensive care unit, known case of any malignancy, immune-compromised state (e.g. HIV), diabetes mellitus, active pulmonary tuberculosis, past history of any chronic respiratory disease, motor neuron disease, multiple sclerosis, stroke, impaired cognition, atrial fibrillation, acute coronary syndrome, myocardial infarction, severe arrhythmia, concurrent serious hepatic disease or renal disease, pregnant or lactating women, patients on immunosuppressive medications, history of hypersensitivity to the trial drugs or their ingredients, depressive illness (before COVID-19), diagnosed psychotic illnesses, substance dependence or alcoholism will be excluded.

**Interventions**

**Intervention Arm (Group-I):** Ayurveda interventions including Agastya Haritaki six grams and Ashwagandha tablet 500 mg twice daily orally after meals with warm water and two sessions of yoga (morning 30 minutes and evening 15 minutes) daily for 90 days, as per the post-COVID-19 care protocol provided in National Clinical Management Protocol based on Ayurveda and Yoga for management of COVID-19 published by Ministry of AYUSH, Government of India.

**Comparator Arm (Group-II):** WHO Rehabilitation Self-Management after COVID-19 related illness for 90 days.

The trial drugs are being procured from a GMP certified pharmaceutical company.

**Withdrawal Criteria:** Participant not willing to continue or non-compliant (less than 80% compliance) with the study procedure; participant develops life threatening complication or any other severe illness because of other pathology which requires urgent treatment; Adverse effect (AE)/ Adverse drug reaction (ADR) necessitating hospitalization. The decision to withdraw a participant from the trial will be informed to the Sponsor and the Ethics Committee within two working days with detailed justification.

**Compliance:** The drug compliance will be assessed at each visit during the follow-up by counting the number of empty containers returned and assessing the approximate quantity of medicines consumed by the patient. Also, drug compliance report form will be provided to the study participants which has to be filled by the participant and submitted to the investigators during the follow-up visit. Similarly, compliance regarding Yoga protocol and WHO Rehabilitation Self-Management guidelines will also be accessed through compliance report form provided to the study participants.

**Concomitant and Rescue Medication:** Participants registered under the trial will be instructed to avoid the use of any other drugs on their own for any ailment and to consult the investigators for any symptom or complaint, or if they feel anything unusual. The investigator will record any medication(s) he/she may prescribe to alleviate their ailments. To alleviate any emergency medical condition, the use of any rescue medication will be permitted as per the discretion of the Investigators. However, the same will have to be documented in the Case Record Form.

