**Outcomes:**

Primary Outcome: Change in respiratory function to be assessed by San Diego shortness of breath Questionnaire, 6-minutes walk test and Pulmonary Function test.

Secondary Outcomes:

- Change in High-resolution Computed Tomography (HRCT) Chest
- Change in Fatigue score assessed by Modified Fatigue Impact Scale
- Change in Anxiety score assessed by Hospital Anxiety and Depression Scale Score
- Change in Sleep Quality assessed by Pittsburgh Sleep Quality Index
- Change in the quality of life assessed by COV19-QoL scale
- Safety of the interventions will be assessed by comparing hematological and biochemical investigations before and after the intervention period and Adverse Event/ Adverse drug reaction

**Timelines for Outcome assessment:** Subjective parameters and clinical assessment will be assessed at baseline, 15^th^ day, 30^th^ day, 60^th^ day and 90^th^ day. Laboratory parameters (CBC, LFT, KFT, HbA1c, Hs-CRP, D-dimer), Pulmonary function test and HRCT Chest will be done at baseline and after completion of study period i.e. 90^th^ day.

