**Blinding:** The study is open-label design. However, the outcome assessor will be kept blinded regarding the study group allocation of the participants.

**Data collection methods:** After informing the participants about the research study as per Patient Information Sheet, written consent (in triplicate) will be taken from the participants before screening them. After screening the participants, the eligible participants will be included in the study and data will be collected in a case record form. The data will be subsequently recorded in an e-format for statistical analysis and record.

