**Data management:**

**Statistical methods:**

The categorical variables in the study data will be summarized as number (percentage) and compared using chi-square test. The continuous data having normal distribution will be represented as mean (SD), and data not following normal distribution as median (min-max). Parametric data will be analyzed by paired t-test and independent sample t-test for within and between group analysis respectively whereas non-parametric data will be calculated by Wilcoxon signed rank test and Mann-Whitney test for within and between group analysis respectively. All the data analysis will be done using the STATA software version 16.1.

**Data Monitoring:** The study will be monitored by Data and Safety Monitoring Board (DSMB). An Interim analysis, if required can be done when at least 25% participants have completed their trial period.

**Ethics Approval:** The study protocol has been approved by the institutional Ethics committees of both the study sites viz., Government Medical College, Nagpur, India and Datta Meghe Institute of Medical Sciences, Wardha, India on 3^rd^ February 2021 and 24^th^ February 2021 (vide EC-CT-2019-0129 and EC/Pharmac/GMC/NGP/2309) respectively. The study will be conducted in accordance with the principles of Declaration of Helsinki and the ICMR’s National Ethical Guidelines for Biomedical and Health Research on Human Participants (2017).

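### Withdrawal for low compliance or a hospitalising adverse event ends participation with no further assessment, which exposes the efficacy and safety comparisons to selective loss of day-90 data

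*Protocol*

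**What the plan says.** In the Protocol, Interventions, the Withdrawal Criteria list four kinds of reason. Two matter most here: "Participant not willing to continue or non-compliant (less than 80% compliance) with the study procedure" and "Adverse effect (AE)/ Adverse drug reaction (ADR) necessitating hospitalization". The scope is set by the sentence that follows the list: "The decision to withdraw a participant from the trial will be informed to the Sponsor and the Ethics Committee". This is withdrawal from the study and not only from treatment.

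The Compliance paragraph of the same section measures compliance differently for different components. Group I drug intake is checked at each visit by "counting the number of empty containers returned and assessing the approximate quantity of medicines consumed by the patient", together with a form that the participant fills in. For the rest, "compliance regarding Yoga protocol and WHO Rehabilitation Self-Management guidelines will also be accessed through compliance report form".

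Under Blinding, "The study is open-label design"; only the outcome assessor is masked.

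Under Outcomes, questionnaires and clinical assessments fall at baseline and days 15, 30, 60 and 90, but "Pulmonary function test and HRCT Chest will be done at baseline and after completion of study period", which means day 90. Laboratory tests follow the same two-point schedule. Statistical methods gives the between-group test: "Parametric data will be analyzed by paired t-test and independent sample t-test for within and between group analysis respectively", with rank tests as the non-parametric alternative. The sample size paragraph allows for 20% dropout.

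**The concern.** Randomisation protects the comparison only if outcomes are sought from everyone randomised. Here two events that occur after randomisation, low compliance and a hospitalising adverse event, end participation, and nothing in the protocol provides for assessment afterwards.

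Both events can depend on the assigned arm. Container counts exist only for the Group I drugs, so a shortfall there can come to light in a way that has no counterpart in Group II. Reactions to the trial drugs can occur only in Group I. Staff who decide on withdrawal are not masked. Both events can also depend on how the participant is recovering.

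Two comparisons are at stake. For efficacy, pulmonary function is part of the primary outcome and has a single post-baseline measurement, at day 90, so early withdrawal loses it entirely. For safety, laboratory values before and after treatment are compared, and those hospitalised for an adverse event would leave that comparison. A statistical analysis plan can choose an analysis set or a missing-data method, but it cannot supply measurements that the protocol stopped taking.

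**Working it through.** **1. What is lost and what is kept, by measure (Outcomes, read with Withdrawal Criteria).**

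| Measure | Scheduled | If withdrawn before day 90 |
|---|---|---|
| Pulmonary function (primary) | baseline, day 90 | no post-baseline value |
| HRCT, laboratory safety tests | baseline, day 90 | no post-baseline value |
| Dyspnoea and other questionnaires; walk test if it counts as clinical assessment | baseline, days 15, 30, 60, 90 | earlier values exist, later ones do not |
| Adverse events | during participation | the triggering event is known, later ones are not |

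This step needs no numerical assumption.

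**2. The plan's own sample size.** Inputs from the sample size paragraph: walk-test improvement of 40 m against 10 m (difference 30 m), SD 50 m, alpha 0.05 (taken as two-sided), power 80%, dropout 20%.

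n = 2 × (1.960 + 0.842)² × 50² / 30² = 43.6, so 44 per group; 44 / 0.8 = 55. The stated 55 per group is reproduced. The allowance keeps power at about 80% with 44 evaluable per group. It does nothing about who is missing. With 110 participants at each of two sites, the trial has 220 participants, or 110 per group.

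**3. Size of a possible shift (illustration only).** Let w be the proportion of an arm withdrawn, and g the mean change among those retained minus the mean change among those withdrawn. The arm mean is (1 − w) × retained + w × withdrawn, so the retained mean exceeds the whole-arm mean by w × g. With no true effect, a comparison of those retained is expected to differ by

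shift = w₁g₁ − w₂g₂, which is (w₁ − w₂) × g when the gap is the same in both arms.

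The document gives neither w by arm nor g, so both are assumed. SE = 50 × √(1/[N(1 − w₁)] + 1/[N(1 − w₂)]); the two-sided false-positive rate uses the normal approximation with N = 110 per group.

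| w₁ / w₂ | g (m) | Shift (m) | False-positive rate |
|---|---|---|---|
| 20% / 20% | any | 0 | 5% |
| 20% / 10% | 10 | 0.10 × 10 = 1.0 | 5.2% |
| 20% / 10% | 25 | 0.10 × 25 = 2.5 | 6.3% |
| 20% / 5% | 30 | 0.15 × 30 = 4.5 | 9.5% |
| 30% / 10% | 50 | 0.20 × 50 = 10.0 | 26% |
| 30% / 5% | 50 | 0.25 × 50 = 12.5 | 38.4% |

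For the last row, SE = 50 × √(1/77 + 1/104.5) = 7.51 m. Against the planned 30 m, the non-zero shifts are 1/30 = 3% to 12.5/30 = 42%. If the withdrawn did better than the retained, g would be negative and the shift would have the same size with the opposite sign.

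More participants do not help: in the 30% / 10%, 50 m case the false-positive rate is 15% at 55 per group and 26% at 110.

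**The case against.** A reader might infer that the comparison is biased in favour of Group I. The document does not support that. It gives no withdrawal rates by arm and no outcomes for those withdrawn. The reverse is also possible: the Background says that people typically recover in 2 to 6 weeks, and eligibility allows a positive test up to 4 weeks old. Some Group I participants might therefore stop tablets and yoga because they feel well, and withdrawing them would count against Group I. The assumption of heavier withdrawal in Group I is also partly a guess. Its regimen is described, but the daily load of the WHO self-management programme is not. The documented asymmetry is narrower: container counts for the Group I drugs only, with yoga and Group II both checked by report form.

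A reader might also infer that withdrawn participants' data are discarded, or that the hospitalising event goes unrecorded. Neither is stated. Values from days 15, 30 and 60 may exist and could be used. Adverse events are an outcome in their own right, and each withdrawal is reported with its justification within two working days.

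Finally, the analysis population may be defined in a statistical analysis plan that is not at hand, so its absence from the protocol is not a fault, and the study is labelled exploratory.

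All of this stands and limits the point. It does not answer the gap in data collection: no assessment is provided after withdrawal, several outcomes have no other post-baseline visit, and masking the assessor does not help with an assessment that is never made.

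**Conclusion.** The point holds as exposure to bias and not as demonstrated bias. Following the protocol as written loses all post-baseline pulmonary function, HRCT and laboratory safety values for anyone withdrawn before day 90, and all later questionnaire, walk-test and adverse event data. The reasons arise after randomisation and can differ by arm. That much rests on the text alone.

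The size rests on assumption. On the values used here the walk-test difference shifts by about 1 to 12.5 m in either direction, and by zero if withdrawal and gap are equal across arms. The upper end needs a gap of a full SD and six times as much withdrawal in one arm as in the other, so it is an extreme and not an expectation. For pulmonary function no size can be given, because the protocol states no planning values for it. The stated sample size is not in error. The exploratory label does not remove the point, because uncollected day-90 data cannot be restored later.

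**What to change.** Amend the Withdrawal Criteria to distinguish ending or altering the study intervention, as the investigator decides, from leaving the study. State that meeting a criterion does not end follow-up. All scheduled assessments and adverse event recording then continue to day 90 for everyone randomised, unless the participant withdraws consent to follow-up. Compare participants in the group to which they were assigned, and use the 80% compliance threshold only to define a supportive per-protocol set. No position is taken on when treatment should be stopped.

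The cost is protocol wording and visits already scheduled for people who would otherwise have been dropped. The estimate may be somewhat smaller. For example, if 20% of Group I were followed but gained none of the 30 m benefit, the expected difference would be 30 × 0.8 = 24 m. Power with complete follow-up would then be about 95% at 110 per group (71% at 55). At 10% the difference is 27 m, with power of about 98% (81% at 55). The 220 participants planned across the two sites can absorb this.

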**Outcomes:**

Primary Outcome: Change in respiratory function to be assessed by San Diego shortness of breath Questionnaire, 6-minutes walk test and Pulmonary Function test.

Secondary Outcomes:

- Change in High-resolution Computed Tomography (HRCT) Chest
- Change in Fatigue score assessed by Modified Fatigue Impact Scale
- Change in Anxiety score assessed by Hospital Anxiety and Depression Scale Score
- Change in Sleep Quality assessed by Pittsburgh Sleep Quality Index
- Change in the quality of life assessed by COV19-QoL scale
- Safety of the interventions will be assessed by comparing hematological and biochemical investigations before and after the intervention period and Adverse Event/ Adverse drug reaction

**Timelines for Outcome assessment:** Subjective parameters and clinical assessment will be assessed at baseline, 15^th^ day, 30^th^ day, 60^th^ day and 90^th^ day. Laboratory parameters (CBC, LFT, KFT, HbA1c, Hs-CRP, D-dimer), Pulmonary function test and HRCT Chest will be done at baseline and after completion of study period i.e. 90^th^ day.

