**Participant Timeline:**

|  | **Study Period** | | | | | |
| --- | --- | --- | --- | --- | --- | --- |
|  | **Enrolment** | **Allocation** | **Post Allocation** | | | |
| **Time points** | **Screening** | **Baseline** | **15^th^ Day** | **30^th^ Day** | **60^th^ Day** | **90^th^ Day**  **(Close out)** |
| **Enrolment:** | | | | | | |
| Information and Informed consent |  |  |  |  |  |  |
| Eligibility evaluation |  |  |  |  |  |  |
| Allocation |  |  |  |  |  |  |
| Intervention: | | | | | | |
| Issue of Trial drug and Yoga Training to Group A |  |  |  |  |  |  |
| Training to practice ‘WHO Rehabilitation Self-Management after COVID-19’ to Group B |  |  | If required | If required | If required |  |
| Medical history and Demographic profile |  |  |  |  |  |  |
| Clinical examination |  |  |  |  |  |  |
| Prakriti (Constitution of body and mind) assessment |  |  |  |  |  |  |
| Assessment of Respiratory function, Fatigue, Sleep, Anxiety and Depression |  |  |  |  |  |  |
| Assessment of Quality of Life (COV19-QoL scale) |  |  |  |  |  |  |
| Laboratory and Radiological Investigations |  |  |  |  |  |  |
| Drug compliance |  |  |  |  |  |  |
| Rescue medication |  |  |  |  |  |  |
| Adverse events |  |  |  |  |  |  |

**Sample size:** The sample size for the study is calculated assuming improvement in 6-minutes walk test by 40 meter in Group I and a change of 10 meter in Group II with a standard deviation of 50 meter based on the results of the previous studies, with 95% Confidence Level (α = 0.05) and 80% power and expecting a dropout rate of 20%. The number of participants to be enrolled in the study should be approximately 55 in each group. Hence, a total of 110 participants will be enrolled in the trial at each study site.

**Recruitment:** The eligible participants will be screened from the patients with post COVID complaints visiting the Out-Patient Department of Government Medical College and Hospital, Nagpur and Datta Meghe Institute of Medical Sciences (Deemed as University),Wardha, Maharashtra, India.

**Randomization:** Statistical package for Social Sciences (SPSS) version 15.0 is used to generate the random number sequences. The participants will be randomized to two study groups in the ratio of 1:1.

**Allocation concealment:** The allocation concealment will be implemented through opaque, sealed envelopes. The allocation sequence will be generated by a statistician, who is not involved with the enrolment process.

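### The primary outcome is three unranked measures with no success rule, and only the walk test is powered

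*Protocol*

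**What the plan says.** The Outcomes section of the protocol gives one primary outcome: "Change in respiratory function to be assessed by San Diego shortness of breath Questionnaire, 6-minutes walk test and Pulmonary Function test". It names no lead measure, no composite, no lung-function parameter and no rule for mixed results.

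On timing, the same section says "Subjective parameters and clinical assessment will be assessed at baseline, 15^th^ day, 30^th^ day, 60^th^ day and 90^th^ day", and for lung function "Pulmonary function test and HRCT Chest will be done at baseline and after completion of study period i.e. 90^th^ day". Lung function therefore has a single post-baseline time point. The questionnaire has four, and so does the walk test if it counts as a clinical assessment. None of the four is called primary.

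The Sample size paragraph uses one of the three measures: "improvement in 6-minutes walk test by 40 meter in Group I and a change of 10 meter in Group II". For that measure it takes an SD of 50 m from earlier work and sets α at 0.05, power at 80% and dropout at 20%. It gives no effect size or SD for the questionnaire or lung function.

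Statistical methods assigns t-tests or their rank-based counterparts according to distribution, without saying which comparison decides the trial. Under Blinding, the trial is open-label, with the qualification: "However, the outcome assessor will be kept blinded regarding the study group allocation of the participants". Study Design describes the trial as exploratory, while Objective(s) sets an efficacy comparison with the WHO self-management programme.

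**The concern.** A primary outcome should tell the reader, before any data are seen, which result answers the main question. Here three different results could do so: a self-reported breathlessness score, a walking distance and an unspecified lung-function measurement. If they disagree, the protocol gives no way to read the trial. The choice could then be made after the results are known, by measure and, for at least one measure, by visit.

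The questionnaire is the most exposed of the three. Participants know their arm and complete it themselves, so a blinded assessor cannot shield it from expectation. As the protocol stands, nothing prevents the efficacy claim from resting on it alone, although the trial was sized on something else.

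**Working it through.** **Inputs from the protocol.** Walk-test difference 40 − 10 = 30 m; SD 50 m; α = 0.05; power 80%; dropout 20%; 1:1 allocation; three measures in the primary outcome. Two-sided testing is assumed, because it reproduces the stated number and one-sided testing does not (35 evaluable, 44 enrolled).

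**1. The plan's own figure.** Per group, n = 2 × SD² × (z₀.₉₇₅ + z₀.₈₀)² / difference² = 2 × 50² × (1.960 + 0.842)² / 30² = 43.6, so 44 evaluable. Allowing for dropout, 44 / 0.80 = 55. This matches the protocol exactly, so the calculation is right for the walk test. It says nothing about the other two measures.

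**2. If any one of the three at p<0.05 were enough.** With independent tests, the chance of at least one false positive is 1 − 0.95³ = 14.3%. The documents give no correlations, so a range is assumed (simulation of three equally correlated normal test statistics; one visit and one lung-function parameter):

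| Assumed correlation | Chance of at least one false positive |
| --- | --- |
| 0 | 14.3% |
| 0.3 | 13.6% |
| 0.5 | 12.5% |
| 0.7 | 10.9% |
| 0.9 | 8.4% |

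If any post-baseline visit could also count, and the walk test follows the clinical-assessment schedule, there are 4 + 4 + 1 = 9 tests. Independence would give 1 − 0.95⁹ = 37.0%, an upper figure. With assumed correlations of 0.3 to 0.5 between measures and 0.5 to 0.8 between visits, simulation gives about 23% to 31%.

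**3. If all three had to succeed at 0.05.** The type I error is at most 5%. Suppose each measure had 80% power, which the protocol supports for the walk test only. Joint power is then 0.80³ = 51% with independent tests, 57% at correlation 0.3, 61% at 0.5 and 66% at 0.7 (simulated). This is well below the planned 80%.

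**4. If all three stay primary with the error rate split.** At α = 0.05/3 = 0.0167 and a standardised walk-test difference of 30/50 = 0.6, the t-test has these powers:

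| Evaluable per arm | Enrolled in total, 20% dropout | Power at 0.05 | Power at 0.05/3 |
| --- | --- | --- | --- |
| 44 | 110 | 79.5% | 64.6% |
| 88 | 220 | 97.7% | 94.0% |

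Both rows are shown because the Sample size paragraph calculates about 55 per group and then assigns 110 participants to each of two sites, which makes 220. To keep 80% walk-test power at 0.05/3 would take 2 × 50² × (2.394 + 0.842)² / 30² = 58.2, so 59 evaluable and 74 enrolled per group (59 / 0.80 = 73.75).

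**The case against.** The strongest counter-argument is that the error inflation depends on a rule the protocol does not contain. A reader might infer that efficacy may be claimed on any of the three measures at well above a 5% error rate. The text does not say so. The three instruments are joined by *and*, which is at least as compatible with requiring all of them. Nor does Statistical methods give a significance threshold; the only 0.05 is in the walk-test calculation. This part of the objection stands: the inflation is conditional on the rule. It does not rescue the definition, because the other reading costs power and the protocol chooses neither.

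Second, a statistical analysis plan may supply a multiplicity method, a testing order or a lung-function parameter. That is fair, and the absence of those items is not the point here. Which variable is primary is something the protocol itself defines. It does so ambiguously, next to a sample size that serves one of the three candidates.

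Third, the study is labelled exploratory. That lowers the expectation of strict error control. It does not remove the problem, given an efficacy objective and a calculation with 5% error and 80% power.

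Two other strong readings should be avoided. The visit gap does not cover the whole primary outcome, since lung function is measured after baseline only at day 90. And error control with three primaries is not simply affordable: that holds at 220 enrolled, but at 110 walk-test power drops to about 65%.

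Finally, the walk test depends on effort, and walkers know their arm. Preferring it rests mainly on its being the measure the trial was sized for; it is not free of expectation effects.

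**Conclusion.** The point holds in this form. The primary outcome is three unranked measures with no success rule. The questionnaire has no primary visit, and neither does the walk test if it follows the clinical-assessment schedule. Only the walk test is powered.

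The size depends on the rule adopted: a false-positive chance of about 8% to 14% if any one measure suffices (correlations 0.9 to 0), or joint power of about 51% to 66% if all three must succeed (correlations 0 to 0.7, 80% power for each). The correlations, and the 80% for the questionnaire and lung function, are assumptions. The protocol does not establish that the trial will run at an inflated error rate; it leaves open which of these two problems it has. Since this decides what the trial may conclude, it should be settled before any comparison by arm is seen.

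**What to change.** Name change in 6-minute walk distance from baseline to day 90, measured by the blinded assessor, as the single primary outcome, tested two-sided at 0.05. List the questionnaire and lung function at day 90 as secondary outcomes. This matches the existing calculation, so 44 evaluable and 55 enrolled per group are unchanged. It needs only new wording in the Outcomes and Statistical methods sections and no new data.

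The cost is that the questionnaire or lung function alone can no longer carry the primary claim. The walk test also remains effort-dependent in an open-label trial, and the report should say so.

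If the sponsor prefers to keep all three as primary, name one lung-function parameter and day 90 for each measure, and control the family-wise error at 5% by Holm or Bonferroni. In that case, state that walk-test power at 0.05/3 is about 94% with 88 evaluable per arm (220 enrolled) but about 65% with 44 (110 enrolled), and say which enrolment total applies.
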